### Analysis of secondary outcomes

#### Quantitative

For the binary secondary quantitative outcomes, we will use similar analytical methods as for the primary outcome. For continuous outcomes, such as facility readiness for change or score on the Person-Centered Maternity Care scale, we will use a cluster-weighted t-test. As in the case of the primary outcome, linear regression models with cluster-correlated standard error estimates will be used to compare the study arms while adjusting for covariates that are differentially distributed between the study arms.

If the proportion of missing data on these covariates is more than 5%, we will use statistical imputation for missing data. Similarly, if the proportion of missing outcome data is small (< 5%), then complete-case analyses will be used. If the amount of missing data for the study outcomes is > 5% or if it is suspected that missingness for the outcome data are not completely at random, based on examination of reasons for missingness, a series of sensitivity analyses for the distribution of missing outcome data will be performed.

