The evidence that birth companionship improves labor outcomes and experience of care has been available for many years. As such, global guidance supports birth companions. The World Health Organization (WHO) states “continuous companionship during labor and childbirth is recommended for improving women’s satisfaction with services;” [14] and a companion of choice is recommended for all women throughout labor and childbirth [15]. The WHO quality of care framework also states that a woman should have access to the social and emotional support of her choice [16]. National polices in Ethiopia, Kenya, and Nigeria support birth companions. However, birth companions are not yet incorporated into routine practice, and women typically labor and give birth alone [11, 12, 17–23]. One study in Ethiopia showed that 98% of women were not allowed to have a birth companion, and another study in Kenya found 78% were not allowed a companion during labor and 84% during delivery [17, 19]. In Nigeria, a study showed that only 29% of mothers experienced companionship during delivery [20].

A 2019 Cochrane review outlined common barriers to facilities adopting birth companionship: health facility policies, provider attitudes, facility infrastructure, and preparation of families and birth companions [24]. Implementation research on birth companions is needed to test interventions in varying clinical settings and cultures that will address these barriers and lead to increased uptake of birth companions in health centers and hospitals. Common barriers identified in the literature that hinder birth companion presence include lack of facility polices, low knowledge of the benefits of birth companionship by providers and families, space and privacy constraints, negative attitudes of providers, and lack of preparedness of families and birth companions [24]. It is unknown whether a health facility’s readiness to change impacts their ability to successfully implement interventions that increase uptake of birth companions [10].

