**Nasarawa**			
1	312	CEmONC	
2	300	CEmONC	
3	135	BEmONC	
4	109	CEmONC	
5	69	CEmONC	
6	64	BEmONC	
7	45	CEmONC	
8	41	CEmONC	
9	37	BEmONC	
10	37	BEmONC	
11	37	CEmONC	
12	36	BEmONC	

We will use a mixed methods approach to assess impact of the birth companion intervention package and measure the study outcomes with exit interviews, health facility register data extraction, in-depth interviews (IDIs), focus group discussions (FGDs), and key informant interviews (KIIs).

There are five data collection periods. We will first conduct a baseline assessment over the course of approximately four weeks, in facilities meeting the inclusion criteria. Health facilities that decline to participate in the study will be replaced by another facility. Facilities will be randomized after the baseline survey in a 3:1 ratio (i.e., for every three facilities that implement the birth companion intervention, one will serve as a control facility). Randomization is stratified by the number of facility deliveries and by country (Ethiopia) or by county or state within a country (Kenya and Nigeria). Intervention facilities will prepare to introduce the birth companion intervention package over the course of approximately two months to facilitate the presence of birth companions during labor, birth, and the postnatal period. Control facilities will continue to provide the local standard of routine care which may or may not include a birth companion. Facilities will not be replaced or reallocated to study arm post-randomization. This study does not place restrictions on facilities or participants regarding participation in other interventions or research.

We will have three quarterly quantitative and qualitative data collection periods, each lasting for approximately one week. We will conduct an endline quantitative survey, approximately 12 months after birth companion intervention initiation. Mothers, birth companions, health care providers, and unit managers in study facilities will have the option to decline to participate in the study.

At the end of the study, control facilities will be supported to implement the birth companion intervention package by staff from an intervention facility that has a birth companion coverage of approximately 50% or higher (see Fig. 2), assuming that one is available. We will provide limited technical and material support during this period.

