#### Exploratory outcomes

6.Score on facility readiness to change.7.Facility-level costs for updates to physical environment of care and other implementation costs.

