#### Consenting providers and unit managers

Providers and unit managers in ANC, labor and birth wards of intervention facilities will be approached for consent for the duration of the study (approximately 16 months) by study staff. Providers and unit managers will be oriented on the study, informed of why they were chosen, their rights as participants, risks, and benefits. Anyone declining consent will not be included in the study. New providers and unit managers will be consented at the time of data collection. All surveys, interviews and IDIs will be administered after consenting the clients. During the baseline survey, providers will be asked to respond to the facility readiness to change survey. For IDIs and FGDs, they will be approached quarterly after the launch of the intervention. For the quantitative feasibility study, providers in the intervention facilities will be approached during the endline survey. Every effort will be made to protect the confidentiality of participants, but due to practical constraints (e.g., size of facility), it may not be possible to guarantee that supervisors will remain unaware of participation.

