### Data collection

#### Quantitative

Pre- and quarterly post-intervention data will be collected from facilities. All women who deliver in the intervention and control facilities during the data collection period and meet the eligibility criteria will be interviewed prior to being discharged. Basic demographic data (age, parity, education, marital status, and socio-economic status) will be collected. Structured questionnaires will be used to assess coverage of birth companion, choice of birth companion (if present) and experience of care. The person-centered maternity score has been validated and is a 30-item scale [26]. It has three sub-scales: (1) dignity and respect, (2) communication and autonomy; and (3) supportive care. Furthermore, we will collect data from providers in all facilitiesto assess the facility readiness to change using a standardized tool. This tool has five context assessment domains: (1) commitment and motivation; (2) ability to implement; (3) internal culture; (4) clinical team functionality; and (5) knowledge and ability to do the intervention. This tool is formulated for health facility staff and leaders. At endline, we will evaluate the feasibility of implementing a birth companion intervention package in intervention facilities. We will also conduct a quantitative analysis at endline to assess the cost associated with implementing the birth companion package.

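### Between-arm analyses are assigned to a readiness score whose only stated measurement precedes randomisation and to a feasibility proportion collected in one arm only

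*Protocol article*

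**What the plan says.** All references are to the protocol article.

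**Readiness.** It is listed under Exploratory outcomes as item 6, "Score on facility readiness to change". Data collection (Quantitative) says "we will collect data from providers in all facilitiesto assess the facility readiness to change using a standardized tool", without giving a time. Consenting providers and unit managers gives the time: "During the baseline survey, providers will be asked to respond to the facility readiness to change survey". Design and setting fixes the order of events: "Facilities will be randomized after the baseline survey in a 3:1 ratio". Analysis of secondary outcomes (Quantitative) then states "For continuous outcomes, such as facility readiness for change or score on the Person-Centered Maternity Care scale, we will use a cluster-weighted t-test", and adds that "linear regression models with cluster-correlated standard error estimates will be used to compare the study arms", with adjustment for covariates that differ between arms.

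**Feasibility.** Outcome 4 is the proportion of providers and unit managers who say that the physical environment supports a birth companion. On its collection, the consent section says "For the quantitative feasibility study, providers in the intervention facilities will be approached during the endline survey". Data collection (Quantitative) likewise places the feasibility evaluation at endline in intervention facilities. Analysis of secondary outcomes gives binary secondary outcomes methods like those for the primary outcome and makes no exception for outcome 4. Analysis of primary outcomes defines those methods as a cluster-weighted chi-square test of intervention against standard care, with a logistic model in which arm is the main predictor.

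**Motivation.** The Background names as unknown whether a facility's "readiness to change impacts their ability to successfully implement interventions that increase uptake of birth companions".

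**The concern.** A between-arm outcome analysis needs a measurement that the intervention could have changed, and it needs that measurement in both arms. As written, readiness lacks the first and feasibility lacks the second.

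For readiness, the t-test would run and return a p-value. Because the score is named as an outcome alongside the Person-Centered Maternity Care score, a reader could take a significant result as an effect of the package, when it could only reflect chance imbalance. For feasibility, the analyst would find no control data and would have to choose an unplanned analysis for a listed secondary outcome.

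The stakes are limited to one exploratory and one secondary outcome. The comparison of birth companion coverage does not depend on either.

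**Working it through.** The plan gives no figure to reproduce on this point. The check sets the timing and arm of each measurement against the analysis assigned to it. A small calculation then shows what the readiness test would yield.

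**1. Measurement against analysis**

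| Measure | When | Where | Analysis assigned | Can it be done? |
|---|---|---|---|---|
| Readiness (exploratory outcome 6) | Baseline survey, the only time stated | All facilities | t-test and linear regression on arm | Computable, but cannot show an effect |
| Feasibility (secondary outcome 4) | Endline | Intervention facilities only | Chi-square test and logistic regression on arm | Not computable |

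Table 4 points the same way for feasibility. Unit managers are eligible only if they are involved in implementing or managing the intervention, which control facilities do not have during the trial.

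**2. What the readiness test yields**

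Inputs: 9 intervention and 3 control facilities per study area (Sample size, Quantitative). Simplifying assumptions: one independent score per facility with a common standard deviation (SD), and no gain from stratification.

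- Expected difference between arms: 0, because allocation comes after the score is fixed.
- Standard error of the chance difference: SD × √(1/9 + 1/3) = SD × √0.444 = 0.67 SD. The simulated value was 0.666 SD.
- Simulation of 40,000 allocations with a two-sample t-test at 0.05: mean difference 0.000 SD, rejection rate 4.9%.
- The primary analysis is run separately by sub-national region. If readiness were handled the same way in the five study areas, the chance of at least one significant result would be 1 − 0.95⁵ = 1 − 0.774 = 22.6%, taking the areas as independent. The article states the regional split only for the primary analysis, so this last step is conditional.

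Sizeable chance differences are therefore ordinary with three control facilities per area, and none of them would say anything about the package.

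**3. What the feasibility test yields**

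There are no control observations. The two-arm table has an empty row, and the arm variable in the logistic model is constant, so its coefficient is not estimable. The intervention-arm proportion can still be estimated, with an interval that allows for clustering by facility.

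**The case against.** **The readiness comparison may be a balance check.** Statistical analysis and power plans a baseline comparison of participants and facilities by arm, and readiness could belong there. This stands in part: a reader might infer that comparing readiness by arm is meaningless in every use, and that goes too far. But the balance check has its own section, whereas the readiness t-test sits under outcome analysis.

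**Readiness may also be measured later.** The data collection section opens by describing data collected before and after the intervention, and its readiness sentence gives no time. A later measurement is therefore not excluded, but none is stated. If one is intended, the article needs to say so.

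**Methods are only said to be similar for binary secondary outcomes.** The primary outcome is to be reported as well as compared, so the reporting half survives for feasibility. That is correct, and no data are lost. The comparison is nevertheless assigned without an exception, and it cannot be carried out.

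**The readiness question may be analysed elsewhere.** A reader might infer that whether readiness predicts uptake will go unanswered. The article does not support that. The question is raised in the Background, it is not in the stated aim, readiness is exploratory, and a predictor analysis could be in the full protocol or the SAP, neither of which is shown. What can be said is that the analysis the article does fix for readiness cannot address it.

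**Consent.** The consent section describes approaching staff of intervention facilities, while readiness is collected from providers in all facilities before arms are known. A reader might infer that control-facility providers answer the survey without consent. Table 4 requires consent from providers at any study facility, so this is an inconsistency of wording only.

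**Conclusion.** The point holds for two outcomes. The arm comparison of readiness has an expected difference of zero and a false-positive rate at its nominal level, so it carries no information about the intervention. This rests on the baseline survey being the only readiness measurement, as stated. The arm comparison of feasibility cannot be computed. This rests on two consistent statements that feasibility is collected in intervention facilities only.

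Both are errors in what the article fixes, not details left to another document. The consequence is modest: no effect on the primary outcome, the sample size or the main inference.

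**What to change.** 1. **Readiness.** Remove it from the outcomes compared by arm. Report it as a baseline facility descriptor, and use it as an exploratory predictor or effect modifier of endline coverage, which is the question the Background raises. If a post-randomisation measurement is intended, state its timing and compare arms on it with adjustment for the baseline score.
2. **Feasibility.** State that outcome 4 is a single-arm endline proportion with a facility-clustered confidence interval and is exempt from the arm comparison.
3. **Consent wording (minor).** Align the consent section with the statement that providers in all facilities answer the readiness survey.

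Any predictor analysis should be labelled exploratory. As an unadjusted, pooled illustration only: with 9 × 5 = 45 intervention facilities, the correlation detectable with 80% power follows from atanh(r) = (1.96 + 0.84)/√(45 − 3) = 0.432, so r = 0.41. Allowing for about five adjustment terms (site and baseline coverage), 2.80/√37 = 0.460 and r = 0.43. Within one area of nine facilities, 2.80/√6 = 1.143 and r = 0.82. None of these allows for noise in facility coverage. The smallest Ethiopian facilities, with 16 births a month, would give about 16 × 7/30 ≈ 4 births in the seven collection days, which would weaken an observed correlation.

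The cost is a few sentences of wording and an exploratory analysis of data already planned. No new data collection is needed unless a later readiness survey is wanted.

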#### Qualitative

Audio recordings of interviews and FGDs will be transcribed from the local language to English by individuals proficient in the local language and English. The transcriptions will be spot checked for quality against the recordings by study staff conversant in both English and local languages used. Thematic analysis will be employed. As qualitative research is a learning experience in the field, emerging themes in the field shall be considered for inclusion in subsequent data collection activities after discussion by senior research management at Addis Continental Institute of Public Health (ACIPH), International Center for Reproductive Health Kenya (ICRHK), and Maternal and Reproductive Health Research Collective (MRHRC). Analysis will be on-going. Coding of textual passages will be done in Atlas-ti or other qualitative data analysis software. Qualitative data analysts will have training and experience in coding of textual information on health topics. The emerging themes will be summarized in tables and other appropriate formats.

### Data management

#### Quantitative data

Data collectors will receive in-depth training on the study objectives, procedures, and ethics by ACIPH, ICRHK, and MRHRC. A detailed manual with SOPs will be prepared and used in training, piloting, and research. The training will also include proper use of tablets and SurveyCTO, which will be used for data entry at the point of collection. There will be daily checks for completeness and consistency of the collected data. The electronic data capturing system will limit data inaccuracies by building in logic, range, and skip-patterns, and minimizing outliers. Investigators will also be supported with ongoing supervision visits from ACIPH, ICRHK and MRHRC.

Data will be de-identified after data collection by ACIPH, ICRHK, and MRHRC and shared with John Hopkins Biostatistics Center for multi-country analysis. De-identified data will be archived according to Bill & Melinda Gates Foundation policies on Synapse or a similar platform. We will also adhere to ACIPH, ICRHK and MRHRC data sharing policies.

#### Qualitative data

ACIPH, ICRHK and MRHRC will also provide training on study objectives, step-by-step training procedures and guidelines of data collection, recording, and transcribing recordings, and ethics of data collection. Audio recordings of interviews and FGDs will be randomly selected and compared against transcripts for data quality monitoring.

No data or safety monitoring oversight is planned for this study. External audits will occur if requested by local regulatory entities. Data security will be carefully and continuously maintained, with limited secure access to data. All study data collection and administrative forms will be identified by coded number to maintain participant confidentiality. All records that contain names or other personal identifiers, such as locator forms and consent forms, will be stored securely. All local databases will be secured with password protected access systems. To the extent possible, we will minimize risks to confidentiality during data collection by directly entering data into the secure database without the use of paper forms. Participant confidentiality will be ensured during FGDs and KIIs by conducting interviews in a secure location, preferably a closed-door room in a health facility, or, in the case of KIIs, within the participants’ offices.

Quarterly study findings will be shared with health care providers. The final study results will be published as scientific articles and reports. No professional writers will be used. Publications arising from this evaluation will follow the recommendations from the International Committee of Medical Journal Editors.

#### Harms

We do not anticipate that this study will result in adverse events. If any unanticipated adverse event or problems occur, the PI will report such occurrences to the JHSPH Institutional Review Board (IRB) and to the local IRBs in Ethiopia, Kenya, and Nigeria, with all reporting and response according to IRB policies and recommendations.

## Discussion

This protocol describes the birth companion intervention and the research in Ethiopia, Kenya, and Nigeria. Despite strong evidence and global recommendation in support of birth companions, many women continue to give birth alone in unfamiliar, and often poor quality, facility settings. This study of a low-cost intervention package will provide important evidence for overcoming common barriers within hospitals and health centers that currently discourage or prevent women from having a birth companion.

### Trial status

This trial is registered with ClinicalTrials.gov with identifier: NCT05565196, first posted October 4, 2022. This trial is currently recruiting. Baseline surveys were conducted in Ethiopia October 10─November 22, 2022 and in Kenya from November 1─December 9, 2022. For Nigeria, we have received ethical clearance and are preparing to conduct the baseline survey. We anticipate reaching study completion in mid- to late-2024.

### Protocol

Version 1.6, September 2023.

## Data Availability

No data is associated with this article. Study data collection tools and protocol can be made available upon reasonable request. Data availability is anticipated to begin on August 1, 2025. All requests should be sent to [contact].

## Abbreviations

ACIPH: Addis Continental Institute of Public Health
ANC: Antenatal care
Crct: Cluster randomized control trial
FGD: Focus group discussion
ICC: Intra-class correlation coefficient
ICRHK: International Center for Reproductive Health Kenya
IDI: In-depth interview
IRB: Institutional review board
JHSPH: John Hopkins School of Public Health
KII Key: informant interview
MRHRC: Maternal and Reproductive Health Research Collective
PI: Principal investigator
SOP: Standard operating procedure
WHO: World Health Organization
